### Data analysis

Descriptive statistics will be used to describe demographic and baseline characteristics of study participants. A generalized estimation equation (GEE) will be used to test the between-group differences. The accepted level of significance for all analyses will be *P* <0.05. Data analysis will be conducted by statisticians who are independent of the research team. Analysis will be conducted using SPSS software (SPSS 12.0 KO for Windows ©).

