## Abstract

**Background:**

Vascular cognitive impairment, no dementia (VCIND) is a condition at risk for future dementia and should be the target of preventive strategies. Preliminary evidence suggests that acupuncture may be a clinically effective intervention for people with early-stage vascular cognitive impairment. We will do a multicenter, 6-month, drug-controlled, nonblinded, randomized, parallel-group trial to determine whether acupuncture is effective for improving cognitive function and quality of life for patients with VCIND.

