### Sample size

According to the previous study, an improvement of ADAS-Cog scores in the treatment group and the placebo group were 1.8 (standard deviation: 5.94) and 0.3 (standard deviation: 6.32), respectively [17]. The difference in scores between the two groups was 1.5. Accordingly, we assume that a difference within 1.5 indicates acupuncture is not inferior to citicoline treatment. Using a non-inferiority design, and assuming a power of 80%, an alpha value of 5%, and a population standard deviation of 5.89, the required sample size is 94 patients in each group. Allowing for 15% attrition, we should recruit 216 patients, with 108 in each group.

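### The trial is sized for non-inferiority with a 1.5-point margin, but the one inferential rule it states, a difference test at P<0.05, never uses that margin

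*Protocol article*

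**What the plan says.** The Sample size section fixes the hypothesis and the margin: "we assume that a difference within 1.5 indicates acupuncture is not inferior to citicoline treatment". It then gives the design inputs: "Using a non-inferiority design, and assuming a power of 80%, an alpha value of 5%, and a population standard deviation of 5.89". These lead to 94 per group, raised to 108 per group (216 in all) for 15% attrition. Whether the alpha is one-sided or two-sided is not stated, and no true difference is given.

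The Data analysis section has one sentence on how the groups are compared, "A generalized estimation equation (GEE) will be used to test the between-group differences", and one on the criterion: "The accepted level of significance for all analyses will be" P<0.05. It mentions no margin, confidence limit or non-inferiority conclusion. Both the margin and the idea of non-inferiority appear only in the Sample size section.

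The Background paragraph of the abstract says the trial is "to determine whether acupuncture is effective for improving cognitive function". The aim in the main Background section is likewise put in terms of effectiveness and safety. The Primary outcome section schedules two ADAS-Cog assessments after baseline, one when treatment ends and one three months later, and does not name either as primary.

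**The concern.** A non-inferiority trial tests the null hypothesis that the new treatment is worse by at least the margin. A test of between-group difference, in its ordinary sense, has zero difference as its null. These are different hypotheses, and a P value for the second does not settle the first. The two sections therefore do not fit together. An analysis that follows Data analysis does not test what the trial was sized on, and one that follows Sample size departs from the criterion set for all analyses.

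The primary conclusion is at stake. If the treatments are truly equal, which is the usual planning assumption for non-inferiority, the stated test gives P>0.05 about 95% of the time. The article does not say what that most likely result would mean. In a trial of this size it would be easy to report it as equal benefit, and that reading has a high error rate.

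**Working it through.** **Inputs.** From the Sample size section: margin 1.5, SD 5.89, power 80%, alpha 5% (sidedness not stated, so one-sided 5% and 2.5% are both shown), 94 per group before attrition, 108 recruited per group, 15% attrition. Evaluable per group: 108 × 0.85 = 91.8, taken as 92. Assumption: a true difference of 0 for the power figures.

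**The plan's own figure.** Two-arm non-inferiority: n per arm = 2 × [SD × (z_alpha + z_power) / margin]².

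- One-sided 5%: 2 × [5.89 × (1.645 + 0.842) / 1.5]² gives 191.
- One-sided 2.5%: 2 × [5.89 × (1.960 + 0.842) / 1.5]² gives 243.

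Neither reproduces 94. The same formula without the factor 2 gives 95.3 at one-sided 5%, or 94.8 with z rounded to 1.64 and 0.84. The step to 108 matches 94 × 1.15 = 108.1. The sample-size shortfall is a separate matter. It enters here only because it determines how the corrected rule performs.

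**Precision.** SE = 5.89 × √(2/n). At n = 92, SE = 0.868 and the 95% half-width is 1.96 × 0.868 = 1.70. This is wider than the margin, so an observed deficit already beyond 1.5 can be non-significant.

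**If non-significance were read as non-inferiority.** At a true deficit of 1.5, 1.5 / 0.868 = 1.727. The chance of two-sided P>0.05 is Φ(1.96 − 1.727) − Φ(−1.96 − 1.727) = 0.592. A rule that compares the confidence limit with the margin passes the same deficit 5% or 2.5% of the time by construction.

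**Power of the margin-based rule at a true difference of 0.** Φ(1.5/SE − z_alpha). At n = 92: Φ(1.727 − 1.645) = 0.53, or Φ(1.727 − 1.960) = 0.41.

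| n per arm | SE | 95% half-width | P(non-significant), true deficit 1.5 | Power at 0, one-sided 5% | Power at 0, one-sided 2.5% |
|---|---|---|---|---|---|
| 92 | 0.868 | 1.70 | 59.2% | 53.3% | 40.8% |
| 94 | 0.859 | 1.68 | 58.5% | 54.0% | 41.5% |
| 108 | 0.802 | 1.57 | 53.5% | 59.0% | 46.5% |

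At a true deficit of 2.0 and 92 per arm, the difference test is non-significant 36.6% of the time. The margin-based rule passes 1.3% (one-sided 5%) or 0.6% (one-sided 2.5%).

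**The case against.** The strongest reply is that this is a journal article with a five-sentence analysis section. The decision rule, sidedness, analysis sets and order of testing may be set out in a full protocol or analysis plan that is not shown. That disposes of any complaint about missing detail, including analysis sets. It does not remove the mismatch, because the article does state a criterion, says that it covers all analyses, and that criterion is not the one on which the trial was sized.

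Four stronger readings are tempting, and the document does not support them.

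- *That the planned analysis cannot establish non-inferiority.* This is too absolute. A GEE supplies an estimate and a confidence interval that can be compared with 1.5, and a significant result favouring acupuncture would itself imply non-inferiority. Nor does the article name zero as the null value, although that is the natural reading.
- *That the investigators will treat a non-significant result as proof of non-inferiority.* No sentence says so. The 59% is the error rate of a possible misreading, not of a stated rule.
- *That acupuncture could be significantly worse while lying within the margin.* At the planned size and SD, a significant observed deficit must exceed about 1.57 points (108 per arm) to 1.70 points (92 per arm), which is already beyond 1.5.
- *That the abstract poses a superiority question.* Its wording is loose. Against a comparator that the Interventions section describes as effective, non-inferiority could be one route to a claim of effectiveness.

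**Conclusion.** The concern stands as a contradiction between two stated rules. The hypothesis that sized the trial involves a 1.5-point margin, the inferential rule for all analyses does not, and no other rule for concluding non-inferiority is given.

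The consequence is conditional. If a non-significant result were taken as non-inferiority, a true deficit equal to the margin would pass about 59% of the time at 92 per arm (54% to 59% across 108 to 92), against 5% or 2.5% under a margin-based rule. These figures rest on SD 5.89, a two-sided 5% difference test, a normal approximation, and a simple two-group comparison that takes no credit for any precision gained from repeated measurements or baseline adjustment.

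Because the defect concerns the primary conclusion, it needs correction. The Trial status section reports that recruitment is under way, so the rule should be settled before outcome data are seen.

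**What to change.** In Data analysis, replace the comparison sentence for the primary outcome with a rule of this form: at [one named primary time point], non-inferiority is concluded if the lower confidence limit from the GEE for acupuncture minus citicoline in ADAS-Cog improvement lies above -1.5. Superiority (lower limit above 0) is tested only after non-inferiority has been met.

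- State the confidence level and match it to the sample-size alpha: a 95% interval for one-sided 2.5%, or a 90% interval for one-sided 5%.
- Name which of the two post-baseline assessments is primary. Without that, the rule cannot be applied.
- State that a non-significant difference is not evidence of non-inferiority.
- Align the aim in the abstract and in the Background section with the non-inferiority hypothesis.
- Recommended, though not part of the contradiction: report the result in both the intention-to-treat and per-protocol sets.

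**Cost.** The rule uses the same model and data, so this part is wording only. The downside must be disclosed. At 92 per arm with a 95% interval, non-inferiority requires acupuncture to be observed better by more than 1.70 − 1.50 = 0.20 points. Power at a true difference of zero is about 41%, or about 53% with a 90% interval, not the stated 80%. The power statement must therefore be corrected too. On the plan's own margin and SD, 80% power needs 191 evaluable per arm (one-sided 5%) or 243 (one-sided 2.5%).

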## Discussion

Acupuncture is a part of Traditional Chinese Medicine and has been used for thousands of years to treat clinical disorders, including stroke-related deficits. However, the possible effects of acupuncture on cognitive function have received little attention or the evidence base is poor. Acupuncture may be effective in treating some neurogenic cognitive or communicative disorders such as autism [18]. The problems associated with cognition issues after stroke continue to be challenged. This study is expected to provide evidence, with high external validity, for the effectiveness and safety of acupuncture treatment on VCIND patients. To our knowledge, this is the first large-scale, multicenter, randomized, controlled trial specifically evaluating acupuncture therapy in VCIND.

The MMSE is a brief and widely used test for screening for cognitive impairment; however, it has been criticized as a poor screening test for VCIND due to insensitivity to visuospatial and executive function impairments commonly involved in patients with cerebrovascular disease [19, 20]. The Montreal Cognitive Assessment (MoCA) evaluates multiple domains of cognition, including visuo-executive, naming, attention, language, abstraction, delayed recall and orientation, but cannot completely replace the MMSE [21]. In our study, global cognitive function will be assessed using the MMSE and the MoCA in the initial screening session.

The trial has some limitations. First, in certain circumstances, it may be difficult to determine whether the cognitive decline is based on vascular factors, Alzheimer’s disease, or both (mixed forms) because AD and VCI can co-occur and interact in a manner [22, 23]. Second, acupuncturists and participants cannot be blinded to the group allocation, although all outcome measures will be administered and collected by an independent researcher to minimize the risk of detection bias. We will carefully discuss residual sources of bias and their potential impact on clinical outcomes when we analyze the study findings.

These results from this trial will provide preliminary evidence about the usefulness and acceptability of acupuncture for patients with VCIND, which will serve as a basis for further research.

## Trial status

This trial is currently recruiting participants.

## Abbreviations

ADAS-cog: Alzheimer's Disease Assessment Scale, Cognitive Subscale
ADL: Activities of Daily Living
AEs: adverse events
CDT: Clock Drawing Test
IADL: Instrumental Activities of Daily Living Scale
MMSE: Mini-Mental State Examination
MoCA: Montreal Cognitive Assessment
TCS: Treatment Credibility Scale
VCIND: vascular cognitive impairment, no dementia.
